**Fig. 2 Fig2:**
[figure not shown]
Graphical display of the active treatment phase

### Statistical analysis

Clinical, demographic characteristics and mood, cognitive, and QoL scores will be tested for any differences at baseline between the two randomized groups using *t test* or *chi-square* test wherever appropriate. The effect size of aTMS will be assessed by the proportion of response rate, which was defined as “Response: ≥50% MADRS score decrease from baseline” and “Non-response: <50% MADRS score decrease from baseline”. “Remission” is defined by score of 10 or less on MADRS score. Changes in mood and other ratings from baseline to each follow-up time point will be assessed with paired *t* test followed by repeated-measures analysis of variance (*ANOVA*)*.* Statistical tests will be two-tailed.

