## Methods

### Objectives

The primary aim of this study is to test the symptomatic efficacy of aTMS trial protocol. The 2nd aim is to compare the symptomatic efficacy of the early-start aTMS treatment group and delayed-start aTMS treatment group in patients with a DSM 5 Major Depressive Episode. The exploratory aim is to test whether the non-responders to a 1-week course of aTMS will have a higher chance of response to a change in aTMS than repeated the same aTMS modality (from 5 Hz L DLPFC aTMS to 1 Hz R DLPFC aTMS).

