
### Sample size calculation

Based on our center’s TMS results to date, patients start TMS treatment with an average MADRS score of 25.4 (SD 7.3), which decreases significantly to 18.4 (SD 9.9) after 2 weeks of treatment with standard rTMS and to 14.1 (SD 10.7) after 4 weeks of treatment. Participants enrolled in the study would be expected to have similar improvements in MADRS with aTMS treatment.

This study is powered to test the primary aim, i.e., a significant reduction in MADRS scores from baseline to end week 3, in the overall study sample. Based on the MADRS scores cited above for baseline (25.4 ± 7.3) and end week 4 (14.1 ± 10.7) time points, detecting a similar significant change after a course of aTMS would require a sample of 12 participants (alpha 0.5, 95% power). However, given the lack of data on the efficacy of aTMS in an Asian population, and to give a better estimate of response and remission rates, we anticipated that 60% of those recruited will drop out before the end of the trial with an unequal allocation ratio of 2:1, we thus aim to recruit 40 subjects in the delayed start arm and 20 subjects in the immediate start arm for a total of 60 subjects.

No prior data exist on the comparative effects of delayed response with immediate treatment of aTMS (or TMS), we will also explore the aim that non-responders to a 1-week course of aTMS will have a higher chance of response to a change in aTMS from L 5 Hz DLPFC TMS to R 1 Hz DLPFC for depression. This study will produce pilot data for 2nd and exploratory aim, informing the power analysis for a future clinical trial if results reject a null hypothesis.

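### Baseline significance tests between the randomised arms answer no question and are insensitive at 20 versus 40; the analyses named for aim 2 use baseline MADRS only through change scores, not as a covariate

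*Protocol article*

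**What the plan says.** The Statistical analysis section states that clinical, demographic, mood, cognitive and quality-of-life data will be "tested for any differences at baseline between the two randomized groups", by t test or chi-square test. It gives no use for the results.

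On outcomes the same section says: "Changes in mood and other ratings from baseline to each follow-up time point will be assessed with paired" t tests, followed by repeated-measures ANOVA. It adds: "Statistical tests will be two-tailed". It names no covariate and no between-group term. Response is defined as a percentage fall from baseline.

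The Objectives section sets the second aim: to "compare the symptomatic efficacy of the early-start aTMS treatment group and delayed-start aTMS treatment group". The Sample size calculation section plans 20 early-start and 40 delayed-start patients, powers only the reduction in MADRS in the whole sample, and treats the second aim as a source of pilot data for a later trial.

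**The concern.** Allocation in phase 1 is by a random sequence, so any difference between the arms at baseline is due to chance. A test of whether it is due to chance has a known answer. What matters for aim 2 is how large the imbalance is and how strongly the variable predicts outcome, and a p-value gives neither. In arms of 20 and 40, a non-significant result is also compatible with an imbalance large enough to matter.

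Early versus delayed start is the only randomised contrast in phase 1. Baseline MADRS is measured on everyone, because entry requires a score of 20 or more, and it is the obvious covariate. Without adjustment, a chance imbalance leaves some error in the estimated difference, and some precision may be lost. The estimate is meant to inform the power calculation of a future trial, so its accuracy matters even though aim 2 is not powered.

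**Working it through.** **Inputs from the Sample size calculation section.** Arms of 20 and 40; baseline MADRS 25.4 (SD 7.3); SD 9.9 after 2 weeks and 10.7 after 4 weeks of standard rTMS ("to 14.1 (SD 10.7) after 4 weeks of treatment").

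**Assumptions.** The baseline–follow-up correlation ρ is not given; 0.3, 0.5 and 0.7 are used. The follow-up SD at the early-versus-delayed comparison is not given; 7.3, 9.9 and 10.7 are used. Alpha is taken as 0.05, two-sided.

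**1. The plan's own figure.** The stated 12 participants for 95% power can be reproduced with a paired t test:
- Change = 25.4 − 14.1 = 11.3.
- SD of change at ρ = 0.5 = √(7.3² + 10.7² − 2 × 0.5 × 7.3 × 10.7) = √89.67 = 9.47.
- Standardised change = 11.3 / 9.47 = 1.19.
- At two-sided alpha 0.05 this needs n = 12 (power 96.3%).

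The printed alpha of 0.5 would give n = 5 at the same ρ, so 0.05 is used below. That misprint is a separate matter.

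**2. Sensitivity of the baseline test.** SE = 7.3 × √(1/20 + 1/40) = 2.00. With 58 degrees of freedom, only an observed difference above 2.00 × 2.00 = 4.0 points (0.55 SD) reaches p < 0.05.

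| Difference | MADRS points | Power of the test | Probability of a chance imbalance at least this large |
|---|---|---|---|
| 0.3 SD | 2.2 | 19% | 27% |
| 0.4 SD | 2.9 | 30% | 14% |
| 0.5 SD | 3.65 | 43.5% | 7% |
| 0.8 SD | 5.8 | 82% | 0.3% |

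Power of 80% is reached at 5.7 points, and 5.7 / 7.3 = 0.78 SD.

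**3. Precision: covariate adjustment against change scores.** Write s₀ for the baseline SD and s₁ for the follow-up SD.
- Change-score variance = s₀² + s₁² − 2ρs₀s₁.
- ANCOVA variance = s₁²(1 − ρ²).
- Example with s₁ = 9.9, ρ = 0.5: change 53.29 + 98.01 − 72.27 = 79.03; ANCOVA 98.01 × 0.75 = 73.51; saving 1 − 73.51/79.03 = 7%.

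| Follow-up SD | ρ = 0.3 | ρ = 0.5 | ρ = 0.7 |
|---|---|---|---|
| 7.3 | 35% | 25% | 15% |
| 9.9 | 17% | 7% | 0% |
| 10.7 | 14% | 4% | 0% |

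At SD 9.9 and ρ = 0.5, the difference detectable with 80% power moves only from 6.9 to 6.7 points.

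**4. Error left by a chance imbalance.** The slope of follow-up on baseline is ρs₁/s₀. With no treatment effect, an imbalance D leaves an error of size (1 − slope) × D in the change-score contrast, making the arm with the higher baseline appear to improve more. For D = 0.4 × 7.3 = 2.92 points:
- s₁ = 7.3: slope 0.3 to 0.7, error 2.0 to 0.9 points.
- s₁ = 9.9: slope 0.41 to 0.95, error 1.7 to 0.1 points.
- s₁ = 10.7: slope 0.44 to 1.03, error 1.6 points down to about zero.

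Adjustment for baseline removes this error.

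**The case against.** The strongest reply is that the article is condensed. The covariates for a secondary, unpowered comparison may be set out in a full protocol or analysis plan that is not shown, and their absence alone would be no finding. That stands, and it limits the second half of the point to what the article does name: within-person paired tests and a repeated-measures ANOVA on change. It does not answer the first half, because the article itself fixes the baseline tests.

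Four stronger readings are tempting, and the document does not support them.
- *That the baseline tests are planned in place of adjustment.* The article gives them no role, neither choosing covariates nor certifying balance.
- *That baseline MADRS goes unused.* It enters through the change scores and the definition of response. Variance savings of 9%, 25% and 49% (ρ² at 0.3, 0.5 and 0.7) arise only against an unadjusted follow-up score, an analysis the article does not plan.
- *That the tests cannot detect imbalance.* A difference of 0.8 SD is found with 82% power. The weakness is for small and moderate differences.
- *That the main result is at risk.* The powered aim is a within-sample reduction, which imbalance between arms does not bias.

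It can also be said that week 1 may be too early for aim 2, since the Background and the Strengths and limitations sections expect delayed response. That stands: choosing the timepoint is a decision about what is being estimated, not mere wording.

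**Conclusion.** The point holds in a limited form. The baseline significance tests serve no purpose and have low power for moderate differences at 20 versus 40. The analyses named for aim 2 do not use baseline MADRS as a covariate.

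The gain from adjustment over change scores is modest and uncertain: from nothing to about a third of the variance, depending on a correlation and a follow-up SD that the article does not give. The SDs of 9.9 and 10.7 come from patients after 2 and 4 weeks of standard rTMS. At the end of week 1 the delayed arm is still untreated, so a value nearer 7.3 is plausible there, but this is not stated. The entry rule of MADRS 20 or more may also lower both the baseline SD and the correlation.

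The protection against a chance imbalance is worth between about zero and 2 points for a 2.9-point imbalance. This is a minor improvement to a pilot comparison. It does not call the primary aim into question.

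**What to change.** 1. Replace the planned baseline tests with a descriptive table by arm (means and SDs, or counts and percentages), without p-values.
2. For aim 2, name a between-arm model of follow-up MADRS with arm as factor and baseline MADRS as covariate, and report the adjusted difference with its 95% CI.
3. State the timepoint. End of week 1 is the natural contrast with an untreated control, because weekly ratings are already planned and the delayed arm has not yet been treated. After that, delayed-start patients continue to active treatment only if they still meet the entry criteria, so a later comparison would no longer set all randomised patients side by side. Given the expectation of delayed response, the sponsor should confirm that week 1 is the intended question.

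The change needs no new patients, visits or measurements. Adjustment costs one residual degree of freedom (57 in place of 58 with all 60 patients). The only substantive decision is the timepoint.

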A blinded, the trained rater will assess mood each week, from baseline to 2 weeks after treatment, using the Montgomery-Asberg Depression Rating Scale (MADRS) scale. MADRS scale is more sensitive to change in patients’ mental condition than Hamilton depression rating scale [44]. The primary outcome is response rate, which are assessed at end of week 4 and week 6. Secondary outcomes include remission rate, Clinician Global Impression –Improvement Scale (CGI-I) and the self-rated Quick Inventory of Depression (QIDS-16). Patient’s cognition will be monitored using the Montreal Cognitive Assessment Scale (MoCA) before and after the 1-week active treatment period and quality of life (QoL) measured by the Quality of Life Enjoyment and Satisfaction Questionnaire – Short Form (*Q*-*LES*-*Q*-SF), assessed at baseline and end of week 2. MoCA is a brief cognitive instrument recommended for screening for cognitive impairment (CI) in patients. Several studies have compared the discriminant abilities of the MoCA and the Mini-Mental State Examination (MMSE) for screening post-stroke CI, and most studies have demonstrated that the MoCA is superior or equivalent to the MMSE for the detection of CI after stroke. Furthermore, the MoCA has been reported to be sensitive to changes in acute temporary CI after mild stroke/TIA, whereas the MMSE is reportedly not [45]. Therefore, in the current study, we use MoCA to assess acute changes in cognitive abilities.

After aTMS treatment, all subjects will then be followed up once a week for 2 weeks and subjects who achieve remission will exit the study.

#### Randomization at phase 2

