Subjects who have not remitted from the 1st active treatment will enter phase 2 treatment. The second randomization will be stratified into three groups based on whether the participant showed <25% improvement in MADRS scores, between 25% and ≤50% improvement in MADRS scores or >50% improvement in MADRS scores. After that, participants in each group will be randomized (in permuted blocks) to either L DLPFC or R DLPFC treatment. The purpose of patient stratification basing on MADRS score before randomization is a method of permuted block randomization, which is a way to randomly allocate a participant to a treatment group, while maintaining a balance across treatment groups. Each “block” has a specified number of randomly ordered treatment assignments depending on the response to the initial aTMS treatment. Randomization will be generated by study team members who are not involved in the treatment. Treatment assignment is determined by treating doctors. Patients, their caregivers, nurse clinicians, and doctors who do the treatment and outcome assessments will be blinded to the randomization.

#### Treatment at phase 2

Subjects who entered phase 2 will receive another 1 week of 5 Hz L DLPFC aTMS (same protocol as above) or aTMS consisting of right DLPFC at 1Hz, 4 treatment sessions a day (each session consisting of 3000 pulses for 12000 pulses a day), every weekday for 1 week. These patients will also be followed up with weekly assessments for 2 weeks after the end of the second round of aTMS. Therefore, participants who receive a total of 1 week of daily aTMS would have received 60000 pulses while those who received a total of 2 weeks of daily aTMS would have received 120000 pulses.

We will use the Magventure X100 to carry out low-frequency R DLPFC. 1 Hz R DLPFC aTMS will take about 4 h a day. Stimulation will be delivered at the right prefrontal cortex (F4 according to the EEG 10/20 system). R DLPFC aTMS will be delivered at 120% of the RMT, as measured at the initial session. Each session will have 300 trains which is equivalent to a consensus protocol of delivering 3000 pulses per session over the L DLPFC [46].

#### Evaluation of clinical response at phase 2

Similar to the outcome assessment during phase 1, mood improvement and subject QoL will be assessed every week during acute treatment by a trained rater (blinded to treatment allocation) using the MADRS scale until 2 weeks after the initiation of 2nd round of treatment.

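### The phase 2 left-versus-right question is worded on ≥50% MADRS response, a poor measure for a very small randomised comparison; an adjusted MADRS difference would serve it better

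*Protocol article*

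**What the plan says.** Objectives (Protocol article) states the exploratory aim: non-responders to one week of aTMS "will have a higher chance of response to a change in aTMS than repeated the same aTMS modality". Sample size calculation repeats this in terms of response and adds: "This study will produce pilot data for 2nd and exploratory aim, informing the power analysis for a future clinical trial".

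Statistical analysis says "The effect size of aTMS will be assessed by the proportion of response rate" and defines response as "Response: ≥50% MADRS score decrease from baseline". It also plans analyses of the score itself: "Changes in mood and other ratings from baseline to each follow-up time point will be assessed with paired" t tests, followed by repeated-measures ANOVA, all two-sided. It names no left-versus-right contrast on the score.

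Under Randomization at phase 2, everyone who has not remitted is stratified by MADRS improvement (below 25%, 25% to 50%, above 50%) and randomised to left or right. A blinded rater then scores mood weekly, "using the MADRS scale until 2 weeks after the initiation of 2nd round of treatment".

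Elsewhere the article leans on the score. The Hypothesis, the summary of outcomes that closes Evaluation of clinical response at phase 2, and the sample size all concern MADRS reduction. Evaluation of clinical response at phase 1, in contrast, says "The primary outcome is response rate, which are assessed at end of week 4 and week 6".

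**The concern.** Phase 2 is the trial's only randomised comparison of two active treatments, and it will be small. The one measure that the article attaches to that comparison is response, a yes/no cut of a score that is already collected weekly under blinding. Three things are at stake.

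- **Information.** A cut discards some of what the score carries, in a comparison that has little to spare.
- **Fit.** The cut is defined from baseline, yet some randomised patients may already be past it.
- **Use.** The results are meant to feed the power calculation of a later trial. Two proportions from perhaps 8 to 19 patients per arm have wide intervals and give no residual SD for planning on the MADRS.

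**Working it through.** **1. Do the planned score analyses answer left versus right?** A paired t test compares a patient with himself or herself and cannot compare arms. The repeated-measures ANOVA is introduced for change from baseline over time, and no left/right factor is named. The sample size concerns the overall sample.

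**2. Who is already a responder at randomisation?** Remission is MADRS 10 or less, so a patient entering phase 2 scores at least 11. To have improved by more than 50% as well, the study-entry score must exceed 11 / 0.5 = 22. The article's mean starting score is 25.4, so such patients are expected, and they have their own stratum. If baseline means study entry, they count as responders before phase 2 treatment starts, and further improvement cannot register. The article does not say whether baseline is study entry or phase 2 entry.

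**3. The plan's own figure.** The only sample size given is 12, for the fall from 25.4 (SD 7.3) to 14.1 (SD 10.7). With an assumed correlation of 0.5, the SD of change is √(7.3² + 10.7² − 2 × 0.5 × 7.3 × 10.7) = √89.67 = 9.47. The mean change is 11.3. A paired t test at two-sided alpha 0.05 then needs n = 12 (power 96.3%), so the figure reproduces. The printed alpha of 0.5 would give only 3 to 8 and looks like a misprint. The trial is therefore sized on the score, and nothing is sized for phase 2.

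**4. Likely size of phase 2** (1:1 allocation assumed). Taking the 4-week figures as a guide, remission is Φ((10.5 − 14.1)/10.7) = Φ(−0.336) ≈ 37%, leaving 63% unremitted.
- No dropout: 60 × 0.63 ≈ 38, or 19 per arm.
- 60% dropout: 60 × 0.4 = 24, and 24 × 0.63 ≈ 15, or 7 to 8 per arm.
- 60% dropout and no remission: 24 / 2 = 12 per arm.

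**5. Cost of the cut in general.** The large-sample efficiency of a cut relative to the mean is φ(z)² / [p(1 − p)]. At p = 0.5 it is 0.637 and at p = 0.2 it is 0.49. At these arm sizes the loss has to be computed directly. The table gives power of the unadjusted t test minus enumerated power of the uncorrected chi-square, cutting the same normal outcome, with lower response rates of 20% to 40%. On an SD of 9.9, d = 0.5 and 0.8 correspond to about 5 and 8 points (5/9.9 and 8/9.9).

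| Per arm | d = 0.5 | d = 0.8 |
|---|---|---|
| 8 | −1.5 to 4.3 | 1.8 to 6.8 |
| 12 | 2.5 to 7.6 | 9.2 to 14.2 |
| 19 | 8.1 to 11.3 | 17.1 to 18.6 |

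**6. ANCOVA against response, by simulation.** Assumptions: start 25.4 (SD 7.3) and end 18.4 (SD 9.9) in the weaker arm; start-end correlation 0.3 to 0.7 (not given in the article); true difference 3 to 8 points; response = end score at most half the start score; two-sided alpha 0.05. Gain in power of ANCOVA over chi-square:

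| Per arm | Situation | Gain, percentage points |
|---|---|---|
| 8 | 60% dropout, then remission | about 0 to 9 |
| 12 | 60% dropout, no remission | about 2 to 20 |
| 19 | remission, no dropout | about 3 to 22 |

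A repeat with fresh random numbers agreed within simulation error. As one example, at 12 per arm with an 8-point difference and correlation 0.5, power is 31% (Fisher), 47% (chi-square) and 58% (ANCOVA). The gain is 11 points over chi-square and 27 over Fisher.

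**7. Where the gain comes from.** In a run of the same 12-per-arm case, an unadjusted t test on the end score gave 46% against 45% for chi-square. There, most of the gain came from adjusting for the entry score. Response as a percentage of the start score already carries some of that information, which is why this result is less favourable to the score than the table in step 5.

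**The case against.** The strongest reply is that the aim is labelled exploratory, yields pilot data and carries no power claim. Chance of response is a legitimate clinical question, and an article may leave the form of the ANOVA to a fuller plan. All of that stands, and it limits the weight of the point. It does not remove it: the article itself chooses response wording for this comparison, and pilot data for a power calculation are better served by a mean difference and a residual SD.

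The inputs can also be challenged, fairly. The 25.4 is a pre-treatment score, not that of non-remitters entering phase 2. The simulation measures response from phase 2 entry, which the article does not specify. An 8-point gap between two active arms exceeds the whole 7.0-point fall (25.4 − 18.4) reported after two weeks of standard rTMS, so the lower gains are the more plausible ones.

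Three stronger readings are tempting, and the documents support none of them.
- *The article abandons the MADRS score.* It does not: it plans score analyses and sizes the trial on the score.
- *The cut costs a fixed, large amount of power, as the efficiencies of 0.49 to 0.64 suggest.* At 8 per arm the gain over chi-square may be nil, and gains near 20 points need the upper end of the assumptions.
- *The same loss applies to the overall aTMS effect size.* That is a single-group quantity, to which a two-arm power figure does not apply.

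The article's two statements of the primary outcome also conflict, but that is a separate matter.

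**Conclusion.** The point holds in a limited form. The left-versus-right question is set on response, no between-arm analysis of the score is named, and response suits a comparison that includes patients already improved by more than 50% poorly. The gain from an adjusted MADRS analysis ranges from about nothing to about 22 percentage points of power. It depends on arm size (8 to 19), true difference (3 to 8 points) and correlation (0.3 to 0.7), none of which the article gives for phase 2. Against Fisher's test the gain is larger, but the article names neither test for this contrast. Power may well be low on either scale at 8 per arm, so the firmer reasons for the change are that it covers every randomised patient sensibly and gives usable inputs for the later trial. It is a worthwhile, cheap improvement and not a threat to the primary aim.

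**What to change.** In Objectives and Statistical analysis, make the phase 2 left-versus-right estimate the between-arm difference in MADRS with a 95% CI. Obtain it from a mixed model on the weekly phase 2 scores (or ANCOVA), adjusted for MADRS at phase 2 entry and the randomisation stratum, in all patients randomised in phase 2. Report response and remission by arm as supporting results, and say which baseline response refers to. Use the adjusted difference and the residual SD as the pilot inputs.

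Two details must be settled with it. First, patients who remit can exit, so later scores will be absent for some of the best outcomes. State how they are handled, for example by keeping all their scores up to exit in the mixed model. Second, name the assessment at which the difference is read. The article ends phase 2 follow-up two weeks after the end of the second course in one place and two weeks after its start in another, and these must be reconciled.

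Cost: no new visits, data or patients. Response becomes supportive for this aim, and the rule for early exits has to be written.

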Although intermittent theta-burst stimulation (iTBS), a FDA-approved novel form of magnetic stimulation is undergoing intensive study as an alternative approach of rTMS [22–24], the original FDA approved protocol for rTMS, the left 10Hz Dorsolateral Pre-frontal cortex (10Hz L DLPFC) protocol, has a larger evidence base to date. However, there is relatively low efficacy of rTMS compared to ECT [25] and the optimal form of rTMS for patients not responding to initial rTMS modality is unclear [26]. More sessions [27], change of rTMS stimulation intensity [28], change from unilateral to bilateral rTMS treatment [29], or use iTBS to treat drug-resistant depression ([30, 31] have been studied but the results are inconclusive. Current clinical practice commonly changes rTMS modality from high-frequency Left DLFPC (L DLFPC) to low-frequency Right DLPFC (R DLPFC) [32], but there is no evidence that this is more efficacious as compared to adding more sessions of the same rTMS. Moreover, although there is a general acceptance that increased dose and duration of TMS is associated with increased efficacy of rTMS [33], there is preliminary evidence of a delayed response to rTMS [34, 35] suggesting that some patients could be treated effectively with a shorter period of treatment given every weekday, then waiting for several weeks for full clinical improvement from the treatment.

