### Strengths and limitations

This trial has several strengths. The delayed start phase will decrease the likelihood of a significant placebo response by subjects who respond to increased attention in a clinical trial. The psychological response elicited by placebos is very specific depending on various factors such as the patient’s expectations, feelings, beliefs, volition, and hope for improvement [52, 53]. Growing placebo response is an important issue of antidepressant therapy for clinical trials involving patients with MDD [54–57]. A recent meta-analysis summarized from 61 large randomized clinical trials (RCTs) suggesting that there is a large placebo response for rTMS trial regardless of the modality of intervention [58]. In our trial, we designed a 1-week delay of treatment to possibly mitigate the placebo effect of active treatment by rTMS. However, it remains unclear whether this delayed-start phase may also reduce the anti-depressant effect of active treatment as some opinions exist that placebo response may be a component of therapeutic response to rTMS in MDD [58]. Patients will receive treatment as usual during the delayed week without coming to rTMS clinic. During the delayed phase, there is still weekly MADRS assessment and this will help patients maintain good adherence with the trial as the patients will keep informed about the study and establish a positive relationship and engagement with clinical staff.

We proposed a 2-week follow-up period after patients have been treated with compact 20 sessions of rTMS. Several open-label large-scale RCTs have shown that some patients with standard treatment of rTMS experienced a delayed response and required 4–6 weeks of stimulation before showing adequate response [12, 59–61]. Similarly, although the accelerated form of rTMS treatment with multiple sessions conducted daily may induce a rapid anti-depressant effect, there are still possibilities that some patients remain non-responding or poor-responding immediately after completion of prescribed sessions of rTMS. Therefore, 2 weeks follow-up period was proposed in this study to allow us to identify this specific group of patients with delayed responses.

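### Phase 2 response has no reference score of its own, so gains from course 1 inflate the within-arm response rates after course 2

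*Protocol article*

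**What the plan says.** The Statistical analysis section gives the only response definition, "Response: ≥50% MADRS score decrease from baseline", and refers every change to the same point: "Changes in mood and other ratings from baseline to each follow-up time point will be assessed with paired" tests and then an ANOVA for repeated measures. It also takes the proportion responding as the effect size of aTMS.

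On timing, the section on evaluating response at phase 1 says "The primary outcome is response rate, which are assessed at end of week 4 and week 6" and "After aTMS treatment, all subjects will then be followed up once a week for 2 weeks and subjects who achieve remission will exit the study". Those who have not remitted go on to phase 2. They are randomised to left or right stimulation within three strata of phase 1 improvement (below 25%, 25% to 50%, above 50%). Phase 2 is assessed in the same manner as phase 1, and no new baseline is named.

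Under Objectives, the exploratory question is given as follows: "test whether the non-responders to a 1-week course of aTMS will have a higher chance of response to a change in aTMS", with repetition of the same modality as the comparator. The Background cites preliminary evidence that some patients respond late and could be treated for a shorter period, "then waiting for several weeks for full clinical improvement from the treatment". The Strengths and limitations section adds that a "2 weeks follow-up period was proposed in this study to allow us to identify this specific group of patients with delayed responses". The Sample size section describes the exploratory results as pilot data for a future power analysis.

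**The concern.** The exploratory question is about response to the second course. A fall measured from the study baseline combines three things: what course 1 had already achieved at phase 2 entry, any late effect of course 1, and the effect of course 2. A patient at 45% improvement is a non-responder when re-randomised, yet one or two points of ordinary fluctuation make that patient a phase 2 responder. This remains true if patients already above 50% are set aside.

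Both phase 2 arms receive a second course, so no arm shows what would have happened without one. A phase 2 response rate within either arm could therefore be taken as the yield of an additional course when part of it is left over from the first. If such rates are used to plan a later trial, its assumptions start too high.

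**Working it through.** **Inputs from the documents.** Standard rTMS MADRS means (Sample size calculation): baseline 25.4 (SD 7.3), week 2 18.4 (SD 9.9), week 4 14.1 (SD 10.7). Trial entry at MADRS 20 or more (Inclusion criteria). Response at a 50% fall and remission at 10 or less (Statistical analysis).

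**Assumptions.** Pre-post correlation r of 0.3-0.7, late drift of 0-2 points, SD of change 4 in phase 2, normal scores, and no effect of course 2. The documents give none of these.

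**1. The plan's own figure.** No figure is given for phase 2. The stated 12 participants for the primary aim reproduce at r = 0.5:
- SD of change = √(7.3² + 10.7² − 2 × 0.5 × 7.3 × 10.7) = √89.67 = 9.47
- standardised change = 11.3 / 9.47 = 1.19
- paired t test, two-sided alpha 0.05, 95% power: n = 12 (power 96.3%). The printed alpha of 0.5 would give 5.

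The means and SDs are thus read as the sponsor used them, and r = 0.5 lies mid-range.

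**2. Timing.** In the early-start arm, course 1 is week 1, follow-up weeks 2-3 and course 2 week 4. The week 4 and week 6 readings of response therefore fall at or after course 2. With only one baseline defined, this supports the study-baseline reading.

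**3. Distance to the response line.** The line is 25.4 × 0.5 = 12.7. The entry score is 25.4 × (1 − improvement). With an inert second course, P(response) = Φ((drift − gap)/4).

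| Improvement at entry | Entry score | Gap | P, drift 0 | P, drift 2 |
|---|---|---|---|---|
| 45% | 13.97 | 1.27 | 37% | 57% |
| 40% | 15.24 | 2.54 | 26% | 45% |
| 25% | 19.05 | 6.35 | 6% | 14% |

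**4. Averaged over non-responders.** Two million patients were simulated with bivariate normal, rounded scores (means 25.4 and 14.1), keeping baseline ≥20, entry score ≥11 and improvement <50%. About 47-54% lie between 25% and 50% improvement, with a median gap of 3.5 points. Across r = 0.3-0.7:
- drift 0: 11-12% labelled responders on the study baseline
- drift 2: 19-21%, against about 4% if scored from phase 2 entry

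If entry scores are drawn from the week 2 figures (18.4, SD 9.9), the same model gives about 9% and 16%. A different model, also starting at 18.4, with entry-to-follow-up correlation 0.7-0.9 and no drift, gives 10-19% on the study baseline against 2-10% from phase 2 entry.

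**5. Effect on left versus right.** Add an assumed true 3-point advantage for one arm, with drift 2 and SD 4. Sample sizes are for 80% power, two-sided 0.05.

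| Outcome | Rates | Difference | Per arm |
|---|---|---|---|
| Response from study baseline | 19-21% v 35-38% | 16-17 points | about 111-124 |
| Response from phase 2 entry | 4% v 12% | 8-9 points | about 153-157 |
| MADRS adjusted for entry score | – | 3 MADRS points | 28 |

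The last row is 2 × (1.96 + 0.84)² × 4² / 3² = 27.9, rounded up.

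**The case against.** Four points can be made for the plan.

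First, the article never says that the phase 2 reference is the study baseline, and a condensed article may leave detail elsewhere. The first part is true. But the article does fix a response definition and its reference point, and offers no other, so this is a definition that fits its aim poorly and not just an omission.

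Second, left versus right is randomised and stratified on phase 1 improvement, the variable that drives proximity to 50%. This stands. A reader might infer that carry-over biases the comparison or pulls the two rates together. It should fall equally on both arms, and step 5 shows the study-baseline rate separating them better than response from phase 2 entry. At a drift of 4.3 points the ordering of sample sizes reverses, but the risk difference on the study baseline is still no smaller (17-18 points against 15).

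Third, a reader might take the centre's fall from 18.4 to 14.1 as the late drift and arrive at 31-34% spurious responders. The documents do not support that. The fall occurred under continuing daily treatment, and subtracting it from a week 4 mean counts it twice.

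Fourth, the article reports late response as preliminary evidence in some patients and provides the 2-week follow-up for them. Nor does it say that a within-arm rate will be read as efficacy of a second course. Both are fair, and the misreading is a risk and not a stated intention. Even with no late effect, though, step 4 leaves 11-12%.

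**Conclusion.** The point holds for within-arm phase 2 response rates and for nothing wider. Read most naturally, the definition credits course 1 gains to course 2. About 11-21% of true non-responders would be labelled responders after an inert second course, or about 9-16% if entry scores follow the centre's week 2 figures. The size rests on the assumed drift, SD and correlations, and on MADRS figures from standard rTMS and not aTMS. The gaps of 1.3, 2.5 and 6.4 points need only the mean baseline and the 50% rule.

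The randomised left-versus-right comparison remains valid. It can be made considerably more sensitive with data already collected. The aim stays exploratory: with 60 recruited and 60% expected to drop out, 60 × 0.4 = 24 remain in total, fewer than even the 28 per arm above.

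**What to change.** In the phase 2 sections and the Statistical analysis section:

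- Define the phase 2 reference as the MADRS at the second randomisation.
- Make the exploratory comparison the left-minus-right difference in MADRS after course 2, adjusted for that score and the randomisation stratum. Name the visit. The phase 2 text ends follow-up both 2 weeks after the end and 2 weeks after the start of the second round, and these statements must be reconciled. Say which score is used for a patient who exits on remission before that visit.
- Keep response from the study baseline as a description of the whole strategy.
- Do not add a 50% fall from phase 2 entry as a main companion outcome. It is insensitive (step 5) and conflicts with the protocol's exit point of MADRS below 11: halving an entry score of 14.0 means reaching 7.0. In the simulation about 78-80% of those entering at 25% to below 50% improvement would be in remission at or before the point where they counted as responders.
- State that phase 2 supports only a left-versus-right comparison, and that within-arm improvement is not evidence that an additional course works. A new reference score removes the phase 1 gain but not a late effect of course 1, so this sentence is needed as well.

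The cost is wording only. The entry score is already needed to form the strata, and no visit or patient is added.
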